## Abstract

**Background:**

Peer-based exercise interventions that cultivate new opportunities for support with a fellow cancer survivor may result in increased exercise volume. It is not clear whether adding qualified exercise professional (QEP) support to peer-based interventions improves health outcomes. Therefore, the purpose of this study is to determine whether breast cancer survivor (BCS) dyads who receive 10 weekly sessions of virtually delivered QEP support have improved outcomes compared to BCS dyads who do not receive QEP support.

**Methods:**

*Participants* Adult BCS with medical clearance for exercise, who have an internet-connected device, and currently engage in < 150 min of moderate-intensity exercise per week. *Intervention* BCS will be matched using evidence-based criteria. The intervention group will receive dyadic exercise information sessions and a program tailored by a QEP for 10 weeks (intervention period) and have access to the QEP for an additional 4 weeks (tapering period). The control will not receive any QEP support. *Outcomes* The primary outcome is post-intervention self-reported exercise volume. Secondary outcomes include device-assessed exercise volume (i.e., Fitbit), social support, and health-related quality of life. *Randomization* 108 participants, matched in dyads, will be randomized 1:1 to the *MatchQEP* or *Match* groups using a web-based scheme. *Statistical analysis* Outcomes will be measured at baseline, post-intervention, post-tapering, and at 12 weeks post-intervention follow-up.

**Discussion:**

The findings from this RCT will determine if matched BCS dyads who receive 10 weeks of virtually delivered QEP support have higher levels of self-report and device-measured exercise, social support, and health related quality of life compared to matched dyads without QEP-delivered exercise guidance. To our knowledge this will be the first study to assess the combined effect of peer- and QEP support on exercise volume. Project findings will inform and optimize intervention methods aimed to increase exercise among BCS through accessible exercise supports.

*Trial Registration*: The study is registered on ClinicalTrials.gov (study identifier: NCT04771975, protocol Version Number: 2, date: July 22, 2021).

**Supplementary Information:**

The online version contains supplementary material available at 10.1186/s13102-021-00341-w.

## Background

One in eight women in Canada will be diagnosed with breast cancer in their lifetime [1]. Despite increasing survival rates [1] and attention to managing the sequelae of breast cancer, survivors face numerous physical and mental health threats during and after primary treatment that impact their daily functioning and health-related quality of life (HRQOL) [2–5]. Exercise is well-established as a safe and feasible means of improving health and wellbeing through all phases of breast cancer survivorship, including for individuals living with metastatic disease [5–13]. There is long-standing evidence from randomized controlled trials (RCTs) involving breast cancer survivors (BCS) that exercise improves physical, mental, and social health indicators linked specifically to HRQOL; and that exercise is associated with reduced risk of cancer recurrence, cancer-specific mortality, and all-cause mortality [5–15]. Cancer exercise guidelines recommend that BCS engage in a minimum of 90–150 min of at least moderate intensity exercise per week and resistance training at least two times per week [16–18]; however, the majority of BCS do not meet these guidelines [19–22].

In addition to the common environmental and health system exercise barriers that people without cancer face, BCS report that the physical effects of breast cancer treatment pose an additional barrier to exercise [20, 23, 24]. Lack of social support and a lack of access to appropriate exercise programming also prevent engagement in exercise among BCS [20, 23, 25, 26]. For survivors in ‘hard to reach’ demographic groups (e.g., young adults, those living in rural communities, and/or in an area with low socioeconomic status), finding age-appropriate, affordable, and accessible exercise support is particularly challenging [25].

Social support is positively associated with exercise among BCS [27–29], but few studies have included a systematic examination of the influence of different sources and forms of support within exercise interventions (e.g., professional support vs. spousal support/caregiver support vs. support from other survivors) [30–32]. The amount and quality of exercise-related support received has focused on either tangible assistance (e.g., people giving you materials or products that help you to exercise), emotional support (e.g., people providing empathy or care when you discuss the difficulties of exercise), informational support (e.g., people providing information on the benefits of exercise), or esteem support (e.g., people providing encouragement that helps you to exercise) [30]. While these different types of support can come from a variety of sources within a breast cancer survivor’s social network (e.g., family, friends, colleagues, trusted health professionals, and support group members), peer-to-peer support external to an existing social network has not been studied in depth. Drawing from existing evidence, peer-based interventions that intentionally cultivate new opportunities for support (i.e., receiving support from a peer that is outside of, or in addition to, one’s existing support network [33]) can result in positive changes to exercise behavior that can match the effectiveness of professionally delivered supports [34, 35]. Furthermore, peer support interventions that can be delivered remotely have been successful in increasing moderate to vigorous physical activity (MVPA) among BCS [36, 37]. Unfortunately, BCS still report unmet needs related to their ability to find an exercise support peer, especially one who shares the lived experience of cancer [38]. BCS also report challenges with accessing support for exercise from qualified health professionals [24, 25].

Online exercise peer matching systems have been developed specifically for women with cancer in an effort to mitigate social support-related barriers to exercise (see ActiveMatch [activematch.ca] and 2Unstoppable [2unstoppable.org]). The peer-to-peer relationship offers unique benefits and is likely to involve different pathways to exercise initiation and maintenance in comparison to professionally delivered exercise support [35]. Nonetheless, even if two survivors are well-matched as exercise peers, this form of peer-to-peer support does not directly address the barrier of a lack of access to exercise guidance from qualified health professionals [39]. Undoubtedly, the relationship between two untrained peers (two survivors) is distinct from the relationship that exists between a survivor and a qualified exercise professional (QEP). As such, the addition of QEP support has the potential to address survivors’ desire for tailored exercise guidance and synergistically enhance the benefits of receiving social support from a well-matched exercise peer. Furthermore, exercise guidelines for cancer survivors specify the importance of supervised exercise programming [16–18], and suggest that QEP support may be most beneficial for BCS who are the least active and who have the most to gain from exercise support [40].

In the current study, the primary aim is to examine the independent effects of matched peers on self-reported exercise volume among BCS in a RCT with one group of dyads assigned to receive QEP support and the other group of BCS dyads not receiving QEP support. Secondary aims include exploring the effects of matched peers on device-measured moderate-vigorous physical activity (e.g., Fitbit), perceived social support, and HRQOL. Actor-Partner Interdependence models (APIM) (Fig. 1) will be used as a framework to study the peer (dyadic/partner) effects and the effects of the intervention (QEP support) over time [41–43]. Also, a strategic assessment of the cost-effectiveness of offering virtually delivered QEP sessions to matched BCS dyads will help to inform and optimize methods of increasing exercise among BCS through accessible exercise supports.

**Fig. 1 Fig1:**
[figure not shown]
Actor-Partner Interdependence Model framework for indistinguishable dyads testing the effects of breast cancer survivor peers on moderate-to-vigorous physical activity (X = Baseline, Y = Post-10 week intervention as primary endpoint)

### Study purpose

The purpose of this study is to examine interpersonal and individual effects of partnering BCS with a peer and a QEP on self-reported exercise volume (MVPA; primary outcome), and device-measured exercise volume (MVPA; Fitbit), social support, and HRQOL (secondary outcomes). Cost-effectiveness and intervention adherence will also be explored as tertiary outcomes. The effects of a peer and QEP-support intervention group, labelled *MatchQEP*, will be compared to a control group of BCS who are matched with a peer, but not a QEP, labeled *Match*.

There are three main research questions and hypotheses (also presented in Table 1):Are there any differences between the *MatchQEP* group and the control group on self-reported MVPA after the intervention (10 weeks post baseline)? Based on the consistent evidence for positive effects of exercise specialists on MVPA, we expect the peers in the *MatchQEP* group to report greater increases in MVPA than the peers in the control group at post-intervention. We expect these differences to be maintained at post-tapering and follow-up data collections.Does exercise peer 1’s exercise volume (minutes of MVPA) at baseline predict exericse peer 2’s exercise volume after the intervention (and vice versa)? A positive peer effect between baseline and post-intervention within the *MatchQEP* group is expected as the QEP is expected to work with the dyads in ways to support each other’s MVPA. In contrast, non-significant or small peer effects are expected to be observed within the control group who receive no QEP support.To what extent does MVPA at baseline predict MVPA after the intervention? The QEP is expected to improve MVPA and the effects are likely to be strongest for the most inactive women. Therefore, the stability of individual differences in MVPA may be lower in the group that has QEP support compared to the control group.

**Table 1 Tab1:** Research questions and hypotheses for the main study effects exploring the impact of partner (i.e., peer) effects and qualified exercise professional (QEP) support on physical activity among breast cancer survivors

Type of effects	Explanation	Hypotheses
Interpersonal effects		
Partner effect _(P1–P2)_	Influence of the peer 1 (P1)'s baseline MVPA on the peer 2 (P2)’s post-intervention MVPA	Positive effect in intervention group, no effect in control group
partner effect _(P2–P1)_	Influence of the P2’s baseline MVPA on the P1’s post-intervention MVPA	Positive effect in intervention group, no effect in control group
Individual effects		
Actor effect _(P1)_	Stability of the P1’s MVPA from baseline to post-intervention	Intervention group < control group
Actor effect _(P2)_	Stability of the P2's MVPA from baseline to post-intervention	Intervention group < control group
Treatment effect _(P1)_	Difference between the P1’s mean post-intervention MVPA of the intervention group and of the control group	Intervention group > control group
Treatment effect _(P2)_	Difference between the P2’s mean post-intervention MVPA of the intervention group and of the control group	Intervention group > control group
Intervention effects		
Adherence	Adherence is established if BCS in the *MatchQEP* group attend at least 7 out of 10 assigned sessions with the QEP Adherence to peer support in both *MatchQEP* and *Match* groups will be established based on the number of times the peers connect (expecting at least once per week for 10 weeks)	Adherence will be established
Cost-effectiveness	Direct costs will be compared between the *MatchQEP* and *Match* groups and between the *MatchQEP* group to traditional QEP services in Canada	*MatchQEP* will be cost-effective

All research questions also align with the secondary outcomes, such that device (e.g., Fitbit) measured MVPA, social support, and HRQOL will be higher among the *MatchQEP* group.

Intervention adherence and cost-effectiveness will also be explored. We expect BCS to adhere to the *MatchQEP* group by attending at least 70% of the sessions [44, 45] and BCS to adhere to the *Match* group by connecting with their partners at least once per week for 10 weeks. We expect the *MatchQEP* group to be cost-effective (e.g., have lower direct costs compared to traditional in person and clinical QEP services in Canada and a favorable incremental cost-effectiveness ratio compared to the *Match* group). The *MatchQEP* group is also expected to report less health care use (e.g., health care facility visits, doctor visits, procedures received, support services used, and loss of work) compared to the *Match* group.

## Methods

### Study design and participants

This is a two-arm RCT with validated outcome assessment measures. The protocol adheres to the CONSORT guidelines (Fig. 2) [46] and SPIRIT recommendations for reporting of clinical trial protocols [47]. Eligible participants are: (1) English-speaking female BCS; (2) diagnosed with primary stage 0–IV breast cancer, at any stage of treatment; (3) living in Canada; (4) aged 18 years or older; (5) medically cleared for exercise; (6) connected to the internet using any device (e.g., computer, tablet or smartphone; preferably with webcam); and (7) currently engaging in less than 150 min of MVPA per week [16–18]. Participants will be excluded from the study if they report any contraindications to exercise, or had recent or have planned surgery of any kind (including reconstructive surgery).

**Fig. 2 Fig2:**
[figure not shown]
Study flow

### Recruitment

BCS will be recruited using digital recruitment materials. Study investigators will send a recruitment email and social media posts to select community-based cancer programs, services, and organizations across Canada for administrators at these organizations to share with their community members. All recruitment materials will include instructions for interested individuals to contact the study team directly. Eligibility will be confirmed by email or phone call by a member of the study team and all eligible participants will provide informed consent prior to enrollment. The University of Toronto’s Human Research Ethics Unit has approved this study (protocol #00038665).

### Sample size

Sample size calculation was carried out based on APIM power analysis for indistinguishable dyads [48]. Specifically, the alpha was set to 0.05 and the sample size estimate is the smallest number of dyads required to detect the effect when power is at least 0.8. Based on standardized regression coefficient effect size estimates (beta; *ß*) drawn from a pilot study of 46 women matched for exercise (23 dyads) assessed over 21 days (i.e., reflecting the *Match* group in the current study), the actor effect size was *ß* = 0.33, the partner effect size was *ß* = 0.28, and the correlation between the two women’s self-report scores on minutes of exercise at baseline was *r* = 0.46. The correlation of the errors was set at 0.30. At minimum, 32 total dyads are needed to have adequate power to detect an actor effect and 43 total dyads are needed to have adequate power to detect a partner effect for a required sample size of *N* = 86. Attrition may be 30% [49], and 11 additional dyads will be recruited for a total sample size of 108 women (54 dyads total across both groups).

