### Intervention

Matching of participants into dyads will be conducted by a research coordinator based on evidence-informed criteria developed in our formative study [50]. For participants to be matched, they must: (1) live in the same time zone, (2) be in the same age range (i.e., within ± 10 years of age), and (3) self-report similar current exercise volume (i.e., within 30 min per week). Beyond these core matching criteria, we will create discrepancy scores based on other personal and cancer-related characteristics, such as cancer stage at diagnosis, treatment status, time since treatment, participants’ family situation (e.g., having a romantic partner and/or children), and exercise preferences (e.g., preferred time of day for exercise) [25, 51] and account for discrepancies in these characteristics in analyses. All participants will receive an ‘Exercise Peer Support Guide’ that provides tips and strategies for supporting their exercise peer [52, 53] and a one-page infographic highlighting current exercise guidelines for cancer survivors [16–18]. All participants will be given a Fitbit wearable activity tracking device, which will be used for device-measured MVPA. Matched exercise peers will be introduced to one another by a research assistant via Zoom (video conferencing platform) prior to the start of the study period. Refer to Fig. 2 for a study flow chart.

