Multiple-group structural equation modeling (SEM) will be used to estimate and test an APIM with two groups (*MatchQEP* vs. *Match*). To address research question 1, the mean post-intervention levels of MVPA (controlling for actor and partner effects) of the two groups will be compared. For research question 2, the average partner (i.e., peer) effects of MVPA from each BCS in the dyad will be estimated within each group [43]. The effects will be tested by comparing constrained and unconstrained models on chi-square goodness-of-fit values. For research question 3, the average actor effects for MVPA among BCS will be estimated for the *MatchQEP* and *Match* groups and will be tested against each other. These analyses will be repeated for device-measured MVPA, social support, and quality of life (secondary outcomes). Measured covariates (e.g., cancer and personal characteristics, partner characteristics and quality of match, therapeutic alliance) will be included in the models as necessary based on their association with the outcomes.

To assess the intervention effects (tertiary outcomes)*,* adherence will be examined based on the number of sessions attended with the QEP in the *MatchQEP* group and on the frequency the peers connected over the duration of the study for both *MatchQEP* and *Match* participants. Cost-effectiveness will be determined by comparing the direct intervention costs between study groups and between the *MatchQEP* group and traditional, in-person QEP services. Additionally, cost-effectiveness of the intervention group, compared to control group, will be calculated based on the intervention costs per participant with respect to changes in the assessed health outcomes. Incremental cost-effectiveness ratios will determine the cost of one unit of change for the investigated outcomes. Mean costs of each category of health resource use (health care facility visits, doctor visits, procedures received, support services used) and loss of work will be calculated for each group and compared for significant differences using *t* tests. All costs will be determined based on current 2021 Ontario Health Care standards in Canadian dollars.

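### The stated 0.8 power holds only for actor and partner effects pooled over both arms; it does not cover research questions 2 and 3, and no power is given for the between-group comparison on the primary outcome

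*Protocol article*

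**What the plan says.** The Sample size section uses a power analysis for an actor-partner interdependence model (APIM) with indistinguishable dyads. It says that "the alpha was set to 0.05" and that the estimate is "the smallest number of dyads required to detect the effect when power is at least 0.8". The effect sizes (actor 0.33, partner 0.28) and the baseline correlation of 0.46 were "drawn from a pilot study of 46 women matched for exercise (23 dyads) assessed over 21 days", a pilot described as reflecting the Match group. The error correlation was set at 0.30. The result is 32 dyads in total for an actor effect, while "43 total dyads are needed to have adequate power to detect a partner effect". With an allowance for attrition, 54 dyads are to be recruited over both groups.

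The research questions are framed differently. Under Study purpose, question 1 asks about differences between MatchQEP and the "control group on self-reported MVPA after the intervention (10 weeks post baseline"). The Statistical analysis section compares the two groups' mean post-intervention MVPA for question 1. For question 2, "the average partner (i.e., peer) effects of MVPA from each BCS in the dyad will be estimated within each group". For question 3, the two groups' actor effects are tested against each other. Table 1 gives the partner-effect hypothesis as "Positive effect in intervention group, no effect in control group".

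**The concern.** A sample size is informative only for the quantity that it was computed for. Here the computation is for a single-group model, whereas the analysis is a two-group model whose questions concern each arm separately or the difference between arms. A reader will naturally take 0.8 as the power of the trial's questions. If it is not, a null result on question 2 or 3 says little, and nobody can tell from the article what size of QEP effect on the primary outcome the trial could detect.

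The inputs also sit badly with the hypotheses. The partner coefficient of 0.28 comes from women who resemble the control arm, yet Table 1 expects no partner effect in that arm.

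**Working it through.** **Inputs (Sample size section):** actor a = 0.33, partner p = 0.28, baseline correlation rx = 0.46, error correlation re = 0.30, alpha 0.05 (taken as two-sided, since the article does not say), power 0.8. Allocation is 1:1 by dyad (Treatment allocation and randomization).

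**Variance of an APIM path.** Outcome and predictor are standardised.
- Residual variance: s² = 1 − a² − p² − 2·a·p·rx = 1 − 0.1089 − 0.0784 − 0.0850 = 0.728.
- For n dyads, each path has variance (s²/4n)·[(1+re)/(1+rx) + (1−re)/(1−rx)] = (0.728/4n)·[1.30/1.46 + 0.70/0.54] = 0.398/n.

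**The plan's own figures, all dyads pooled.**
- Actor at 32 dyads: SE = √(0.398/32) = 0.112; 0.33/0.112 = 2.96; power = Φ(2.96 − 1.96) = 0.84.
- Partner at 43 dyads: SE = √(0.398/43) = 0.096; 0.28/0.096 = 2.91; power = Φ(0.95) = 0.83.
- With the noncentral t, 0.8 power needs 30–31 and 41–42 dyads. Simulation (4,000 runs) gives power of 0.80 for the actor effect at 32 dyads and 0.79 for the partner effect at 43.

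The stated 32 and 43 are therefore reproduced to within 2 dyads as pooled totals.

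**Question 2, partner effect of 0.28 within one arm (43/2 = 21.5 dyads).**
- SE = √(0.398/21.5) = 0.136; 0.28/0.136 = 2.06; power = Φ(0.10) = 0.54. The noncentral t gives 0.52, and simulation 0.47–0.50.
- With all 54 dyads (27 per arm) and no dropout: 0.59–0.64, about 0.6.
- Power of 0.8 needs about 41–43 dyads in each arm, or 82–86 in total.

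**Question 2 read as a between-group difference, 0.28 versus 0.**
- SE = √(2 × 0.398/21.5) = 0.192; 0.28/0.192 = 1.46; power = Φ(−0.50) = 0.31 (simulation 0.27). With 54 dyads: 0.34–0.37.
- Power of 0.8 needs about 160 dyads in total.

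**Question 3, actor difference.** The protocol gives no expected difference. The extreme case takes the full 0.33 in Match and 0 in MatchQEP.
- 0.33/0.192 = 1.72; power = Φ(−0.24) = 0.40 (simulation 0.37). With 54 dyads: 0.45–0.48.
- About 116 dyads in total are needed, and more for any smaller difference.

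**Question 1, difference in means.** No effect size or SD is given, so power cannot be computed. The detectable difference can be, in SD units of post-intervention MVPA, using dyad means with variance s²(1+re)/2.
- 43 dyads: SE = √(0.728 × 1.30/2 × 2/21.5) = 0.210; (1.96 + 0.84) × 0.210 = 0.59 SD.
- 54 dyads: SE = 0.187; 0.52 SD.
- Under assumed differences of 0.3, 0.4, 0.5 and 0.6 SD, power at 43 dyads is 0.30, 0.48, 0.66 and 0.82.

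**Consistency of the partner input with Table 1.** As an assumption, let the partner effect be 0.28 in MatchQEP and between 0 and 0.10 in Match. The pooled coefficient is then 0.14 to 0.19.
- 0.14/0.096 = 1.46, power about 0.3 (simulation 0.27).
- 0.19/0.096 = 1.98, power about 0.5.

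Under that reading, even the pooled test misses 0.8.

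**The case against.** Several counter-arguments have force.

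- **Sizing on peer effects has a source.** The Background states a primary aim about the independent effects of matched peers, so powering a partner coefficient follows from it. That explains the choice. But the Abstract's purpose and question 1 point to the group comparison, and the article does not reconcile the two. Even on the peer-effect aim, question 2 is asked within each group, not in a pooled sample.
- **A reader might infer that question 1 is shown to have less than 0.8 power.** The documents do not support that. The Sample size section attaches 0.8 only to actor and partner effects, and question 1 would reach 0.8 if the true difference were about 0.59 SD or more. What can be said is that no power was calculated for it.
- **A reader might infer from Table 1 that question 2 will be judged by significance in one arm and not in the other.** The Statistical analysis section instead plans chi-square comparisons of constrained and unconstrained models in a multiple-group framework. A cross-group equality constraint is a natural reading, but the article does not say which paths are constrained. On either reading, power is well below 0.8.
- **The conflict with Table 1 is softer in the text**, which allows small or non-significant control-group effects, and nothing caps the MatchQEP effect at 0.28. This is why the pooled figures of 0.3 to 0.5 are marked as an assumption.
- **A reader might infer that the matching rule invalidates the 0.46.** Peers must "self-report similar current exercise volume (i.e., within 30 min per week") while all are under 150 min, which could raise the baseline correlation. But the pilot women were also matched for exercise, the baseline assessment comes after the report used for matching, and the size of any rise depends on an assumed distribution and measurement error. At r = 0.55 (an assumption), pooled partner power is still about 0.80. This merits at most a sensitivity check.

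A separate analysis plan could clarify the tests, but it cannot make 43 pooled dyads power a within-arm or between-arm test.

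**Conclusion.** The point stands: the basis of the sample size does not match the planned analysis. For question 2 (about 0.5 within an arm, about 0.3 between arms) and question 3 (at most about 0.4), power at the protocol's own coefficients is clearly below 0.8, and retaining all 54 dyads does not change that. For question 1 the defect is that no power or detectable difference is given; the 0.59 SD (0.52 SD at 54 dyads) shows what the design can detect.

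These figures assume the pilot's coefficients and correlations, equal residual variance in the arms, two-sided testing and no added covariates. Question 2 would reach 0.8 within MatchQEP only if its partner effect were well above 0.28.

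**What to change.** - State in the Sample size section that the 0.8 power applies only to actor and partner effects pooled over both arms.
- Name question 1 (MatchQEP minus Match, self-reported MVPA at week 10) as the single primary hypothesis, reconcile this with the primary aim in the Background, and report its detectable difference: about 0.59 SD at 43 dyads and 0.52 SD at 54.
- Label questions 2 and 3 secondary or exploratory, and give their actual power.
- Specify that the constrained-versus-unconstrained comparison for question 2 sets the partner path equal across groups.
- Reconcile the use of 0.28 from a Match-like pilot with Table 1's hypothesis for the control group.
- Optionally, add a sensitivity check on the baseline correlation, marked as assumption-based and including r = 0.55.

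The cost is rewording of the sample-size and analysis sections and a less favourable stated power. No additional participants are required.
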